### Sample size

This is the first trial to compare CT-PTSD (or any other treatment) to routine care in NHS CAMHS and youth mental health settings for children and young people with PTSD following multiple trauma exposure. While two waiting-list controlled trials have been conducted of the CT-PTSD treatment package in research clinics,^34 35^ no UK trials have evaluated the effectiveness of routine care for the treatment of PTSD in young people with multiple trauma exposure, or the effectiveness of CT-PTSD as delivered by therapists working in routine clinical settings. As such, no reliable estimates of effect size are available. An attempt was made to estimate likely effect size based on meta-analyses of existing psychological therapies for PTSD in children and adolescents. The waiting-list controlled effect size of CT-PTSD was greater than 1.2 in each of the studies to have examined this intervention to date.^34 35^ The Cochrane meta-analysis of treatments for PTSD in children and adolescents^10^ yielded an effect size of 1.05 for all psychological therapies versus control conditions, whereas for CBT versus control conditions, the effect size was 1.34. However, these effect sizes are likely to overestimate the efficacy of CBT; few studies were included in the headline analyses, and those that were included were waiting-list controlled, rather than using an active control condition (eg, TAU or other interventions that involved clinician/therapist contact). A high-quality trial of another psychological therapy (prolonged exposure, a form of TF-CBT) for adolescent girls with PTSD following sexual abuse, that used supportive counselling as a control intervention, yielded a controlled (ie, between groups) effect size of 1.0.^39^ An alternative meta-analysis,^60^ including a broader range of studies to evaluate CBT in youth with PTSD (many of which used active control treatments such as supportive counselling) suggested a controlled effect size of around 0.67; a more recent meta-analysis^61^ suggested an effect size for TF-CBT of 0.79. The more conservative effect size estimate of 0.67 was used for the proposed trial.

In order to have 90% power to detect a between groups effect size of 0.67 (two-tailed t-test, 0.05 significance level), a sample size of 96 (48 participants per group) is required; a combined sample size of 96 would have 80% power to detect an effect size of 0.58 (two-tailed t-test, 0.05 significance level). In order to account for drop-out (estimated at 20%), 120 participants will be recruited.

### Recruitment

Participants will be recruited from NHS Trusts in England and Wales. Clinicians in participating teams will be encouraged to contact the trial team to discuss potential participants to ensure that they meet inclusion criteria. If a child or young person appears eligible, the clinician will share information with the participant and their family about the study who will be given at least 48 hours to decide whether they wish to participate. Consenting families will be contacted by the trial team to discuss further and to arrange baseline assessments; trial eligibility will be confirmed following this assessment. Children and young people will not be able to enter DECRYPT (Delivery of Cognitive Therapy for Young People after Trauma) unless a therapist within the team is available to offer CT-PTSD and another clinician/therapist is available to offer TAU, that is, TAU cannot involve a waiting-list.

## Methods: assignment of interventions

### Allocation

Following pretrial assessments, consenting participants will be randomised to study arms stratified by CRIES-8 score (17–28, 29–40) and site (ie, NHS Trust). This cut-off for stratification was based on data from an unpublished pilot study that preceded DECRYPT, where the mean score for study participants was 28.75. An online randomisation service managed by NCTU will assign allocation to groups. Allocation is by preset lists of permuted blocks with randomly distributed block sizes (determined by the trial statistician). The lists will be generated by the Data Management Team at NCTU. The trial manager will enrol participants. Following randomisation, participants, their clinical team and their GP will be notified of their allocation by the trial manager. See figure 2 below for the Consolidated Standards of Reporting Trials diagram.

**Figure 2 F2:**
[figure not shown]
Trial Consolidated Standards of Reporting Trials diagram. CT-PTSD, cognitive therapy for post-traumatic stress disorder; TAU, treatment as usual.

### Blinding

Trained assessors collecting post-treatment and follow-up data will be blinded to group allocation. These assessments will be undertaken by trained assessors with no other role in the trial. Following allocation to CT-PTSD or TAU, all participants in the study, their care coordinator/referrer and clinical team (if applicable) are asked not to reveal the group to which the participants were randomised to the trained assessor.

## Methods: data collection, management and analysis

### Data collection methods

Quantitative outcome variable data will be collected using paper forms and entered electronically on to the trial database or online. Qualitative data will be collected using face-to-face interviews, or where this is not possible telephone or video-call interviews. An appropriately trained individual will undertake semistructured interviews with participants and their families after treatment has been completed. For participants who have withdrawn from treatment or the trial but consent to taking part in a qualitative interview, this will be completed when appropriate. Interviews will be audio-recorded and transcribed verbatim, with all identifying information removed.

### Data management

To maintain confidentiality, each participant will be given a unique trial Participant Identification Number (PIN). Data will be entered under this identification number onto the central database stored on the servers based at NCTU. The database and coding frames have been developed by the Clinical Trial Manager in conjunction with NCTU. The database software provides a number of features to help maintain data quality, including maintaining an audit trail, allowing custom validations on all data, allowing users to raise data query requests and search facilities to identify validation failure/missing data. After completion of the trial, the database will be retained on the servers of NCTU for ongoing analysis of secondary outcomes.

### Statistical methods

A full statistical analysis plan will be written and agreed with the Data Monitoring Committee (DMC) and Trial Steering Committee (TSC) prior to database lock and any data analysis. This plan will be amended only with agreement of the former two committees.

Our primary analysis will compare CT-PTSD with TAU on CRIES-8 scores at post-treatment. The primary analysis will be on the intention-to-treat principle: that is, all participants will be followed up for data collection irrespective of adherence to treatment and will be analysed according to group allocation rather than intervention received. Assuming a normal distribution (potentially of transformed values), a linear model will be constructed. This will include recruiting site (as a random factor), CRIES-8 at baseline (as a covariate) and any factors considered prognostic and determined in advance of any analysis, together with treatment arm as a fixed effect. Analysis of other secondary outcomes, and of putative moderators and mediators, will be considered exploratory.

The primary intention-to-treat analysis is intended to provide inferences regarding the effectiveness of the intervention overall not to provide inferences regarding the causal effect of the intervention itself, but on the intervention as deployed in ‘real life’. Statistical significance will be set at the conventional (two-tailed) 5% level and all parameter estimates will be presented with 95% CIs. Analyses will be carried out by the trial statistician blinded to group identity, (ie, ‘subgroup’ blind). There are no plans for interim efficacy or subgroup analyses. Analyses will be carried out in SAS (currently V.9.4).

Mediation and moderation analyses will be undertaken following the procedures outlined by Kraemer and colleagues.^62^ As with all our secondary analyses, these will be considered exploratory.

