### Interventions

*CT-PTSD*. CT-PTSD for PTSD is a structured, fully manualised^33^ psychological treatment delivered in an individual format for children and adolescents. The proposed frequency and duration of treatment is up to 15 treatment sessions (typically 10–12, of 60–90 min duration).

CT-PTSD involves several core elements: psychoeducation, with an emphasis on the role of cognitive processes in the onset and maintenance of PTSD; narrative work and imaginal reliving to help develop a coherent trauma narrative; cognitive restructuring (to reframe the meanings and interpretations associated with trauma and its aftermath), and coping management (eg, addressing maladaptive strategies such as thought suppression, rumination and safety-seeking behaviours). Up to three sessions will be allowed for stabilising other comorbid conditions and difficulties (eg, depression or self-harm).

CT-PTSD will be delivered by NHS CAMHS/youth mental health service therapists who will have completed training in CT-PTSD by a member of the trial team. Trial therapists who deliver CT-PTSD must have an appropriate professional qualification (eg, as a nurse, occupational therapist, clinical psychologist, social worker, psychiatrist or British Association for Behavioural & Cognitive Psychotherapies-registered cognitive–behavioural therapist) and be approved by their local site principal investigator to act as a trial therapist. Individual teams will nominate staff members to complete the CT-PTSD training.

CT-PTSD will be delivered wherever is permitted and feasible for local therapists (eg, in NHS mental health clinics, local general practitioner (GP) surgeries, at home). Supervision will be provided by a clinical psychologist from the trial team. Following the completion of a course of CT-PTSD, usual NHS care arrangements will apply for participants in this arm.

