#### TAU

Mental health professionals and others involved in the care of the participants in the TAU arm will be encouraged to provide whatever help they deem necessary, for example, general clinical management, supportive counselling, family therapy, medication. TAU must involve an active treatment, that is, it cannot involve being on a waiting-list. Since TF-CBT has been a recommended treatment for PTSD in youth in the UK since 2005,^25^ no therapists in the TAU arm were prevented from delivering this intervention; they were not, however, trained by the research team to deliver the CT-PTSD intervention. Therapist contact in the TAU arm would not be prescribed by trial participation in any way, with one exception: the participants will receive no contact with the trained trial therapists delivering CT-PTSD, and their therapist/clinician will not receive supervision for that case from a trained trial therapist.

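### The sample size makes no allowance for therapist clustering, and the listed primary model accounts for site but not therapist, although different clinicians deliver the two arms

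*Protocol article*

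**What the plan says.** **Analysis.** Under Statistical methods, the primary comparison of CRIES-8 after treatment uses a linear model: "This will include recruiting site (as a random factor), CRIES-8 at baseline (as a covariate) and any factors considered prognostic", with treatment arm as a fixed effect. Site is the only random term. The section promises a full statistical analysis plan before database lock; it is not at hand.

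**Sample size.** "In order to have 90% power to detect a between groups effect size of 0.67", the article requires 96 participants, 48 per group, by a two-tailed t-test at the 0.05 level. It adds that "a combined sample size of 96 would have 80% power to detect an effect size of 0.58", and then: "In order to account for drop-out (estimated at 20%), 120 participants will be recruited". No ICC, design effect, number of therapists or caseload appears.

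**Who treats whom.** Under Interventions, "CT-PTSD will be delivered by NHS CAMHS/youth mental health service therapists who will have completed training in CT-PTSD"; the format is individual, and each team nominates the staff to be trained. Under TAU, "the participants will receive no contact with the trained trial therapists delivering CT-PTSD". Under Recruitment, a child can enter only if the team has one therapist free for CT-PTSD and a different clinician free for TAU.

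**The concern.** Because the two arms have different clinicians, therapist is nested within arm. Participants who share a therapist may have correlated outcomes. That variation does not cancel when the arms are compared; it adds to the variance of the arm difference.

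A random site effect does not deal with this. Randomisation is stratified by site, so each site contributes to both arms and its effect largely drops out of the comparison. Therapist variation sits inside arm within site and stays in.

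At stake are the width of the primary confidence interval and the 5% error rate. The Objectives section names therapists' ability to deliver CT-PTSD in this setting as a significant uncertainty and expects the trial to inform a later definitive one. A model with no therapist term leaves that uncertainty out of the standard error, and the interval carried forward would be too narrow.

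**Working it through.** **Inputs from the article (Sample size):** two-sided alpha 0.05, standardised difference d = 0.67, n = 48 analysed per arm, drop-out 20%.

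**Assumptions (not in the article):** therapist ICC, patients per therapist m (equal caseloads), and whether one or both arms are clustered.

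**Step 1. Reproduce the stated figures.** With SD = 1 and independent outcomes, the noncentrality is d / √(2/n) = 0.67 / √(2/48) = 3.28 on 94 df, which gives power 0.901. With 47 per arm it is 0.895, so 48 is the minimum. At d = 0.58 power is 0.803. Recruitment is 96 / 0.8 = 120. All stated figures reproduce, so they contain no clustering allowance.

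**Step 2. Add therapist clustering.**
- Design effect in a clustered arm: DE = 1 + (m − 1) × ICC.
- Average over arms: k = (DE + 1)/2 if only CT-PTSD is clustered, k = DE if both arms are.
- Power: noncentrality 3.28 / √k, noncentral t on 94 df.
- Correct interval width relative to one that ignores therapist: √k.
- Approximate type I error when therapist is ignored: 2 × P(Z > 1.96 / √k).

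Results at ICC 0.05:

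| m | DE | Clustered | k | Interval factor | Type I error | Power |
|---|---|---|---|---|---|---|
| 2 | 1.05 | CT-PTSD only | 1.025 | 1.01 | 5.3% | 0.894 |
| 2 | 1.05 | both | 1.05 | 1.02 | 5.6% | 0.887 |
| 4 | 1.15 | CT-PTSD only | 1.075 | 1.04 | 5.9% | 0.880 |
| 4 | 1.15 | both | 1.15 | 1.07 | 6.8% | 0.858 |
| 8 | 1.35 | CT-PTSD only | 1.175 | 1.08 | 7.1% | 0.850 |
| 8 | 1.35 | both | 1.35 | 1.16 | 9.2% | 0.798 |

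Range over ICC, both arms clustered: at ICC 0.02, power is 0.896, 0.884 and 0.861 for m = 2, 4 and 8; at ICC 0.10 it is 0.872, 0.813 and 0.703. Unequal caseloads raise the design effect: with m = 4, a caseload coefficient of variation of 0.6 and ICC 0.05, DE = 1 + ((1 + 0.36) × 4 − 1) × 0.05 = 1.222.

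**Step 3. Does adjusting for site remove it?** A simulation assumed 6 sites, a site share of variance of 0.03, a baseline correlation of 0.4, therapist ICC 0.05 and therapist clusters in both arms, with 4,000 runs per setting. The analysis adjusted for site (as fixed indicators) and baseline, but not therapist. Type I error was 0.057, 0.074 and 0.100 for m = 2, 4 and 8, and coverage of the 95% interval was 0.940, 0.928 and 0.890. Site adjustment does not remove the effect. The errors are slightly above the table because, once site and baseline variance are taken out, therapist is a larger share of what remains: 0.05 / (1 − 0.03 − 0.16) = 0.062.

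**Step 4. Credit the baseline covariate.** The t-test calculation ignores it. With an assumed baseline-outcome correlation r, the variance of 1 falls to 1 − r². Unclustered power is then 0.926 at r = 0.3 and 0.963 at r = 0.5. For the uneven caseload above (DE 1.222), with the therapist component not reduced by the covariate, a clustered arm has variance (1 − r²) + 0.222. At r = 0.3 that is 0.91 + 0.222 = 1.132. Power for r = 0.3 to 0.5 is 0.895 to 0.938 with CT-PTSD only clustered, and 0.863 to 0.909 with both arms clustered.

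**The case against.** - **The model already handles clustering.** In part. A reader might infer that the primary model treats all outcomes as independent; it does not, since site is a random factor. The gap is therapist only.
- **The 90% is right.** It is, on its own terms. A reader might infer a miscalculated sample size, or that 90% power is not delivered on the stated assumptions. Step 1 shows otherwise: power falls only under added assumptions that the article does not contain.
- **Baseline adjustment offsets the loss.** It may, so the net direction for power is not known and it cannot be said flatly that power is overstated. The offset does not repair the interval width or the type I error.
- **Caseloads may be tiny.** The article gives no therapist count, and teams across NHS Trusts in England and Wales each nominate staff. Many therapists with one or two cases each is compatible with the text, and the effect is then very small.
- **TAU may have no single therapist.** TAU is not prescribed and may involve several professionals. The figures with both arms clustered are therefore the less well supported.
- **The analysis plan may add a therapist term.** It may. But the article does not leave the random structure blank: it names site, and a therapist random effect is not what one would normally understand by a prognostic factor. The independence assumption in the power statement is already fixed.

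**Conclusion.** The point holds conditionally. The article separates therapists by arm, sizes the trial as if outcomes were independent, and lists a model with a random effect for site only. Analysed as listed, the interval is too narrow and the type I error exceeds 5% whenever the therapist ICC is above zero and therapists treat more than one participant.

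The size depends on assumptions that the documents do not supply. At ICC 0.05 it runs from negligible with two patients per therapist to a type I error of roughly 7-9% with eight. The error rate and interval width are the firm part. The power part is a missing statement of assumptions, and neither a shortfall nor a need to recruit more participants is established. The matter is worth settling before analysis because the remedy is cheap.

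**What to change.** **Analysis.** Record an anonymised therapist code for each participant. Prespecify a therapist random effect in the CRIES-8 model alongside site and baseline, at least for the CT-PTSD arm (a partially nested model), with small-sample degrees of freedom such as Satterthwaite or Kenward-Roger. Add clustering by main TAU clinician as a sensitivity analysis where one can be identified. Requiring separate therapist variances in both arms for the primary model would ask too much of about 96 participants. State a rule for participants who never start treatment but remain in the intention-to-treat set.

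**Sample size.** Say that the 90% assumes independent outcomes and no baseline adjustment, and give power over a stated range of therapist ICC and caseload. No change in recruitment is needed.

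**Cost.** One data field and some analysis-plan wording. Contacts are already to be collected from therapists, clinicians and service records for the economic evaluation, but that section does not mention a therapist identifier, so the field must be added. The interval becomes slightly wider, and the therapist variance will be imprecisely estimated. If it is estimated at zero, the result essentially returns to the planned model. Caseload patterns, or a term fitted in one arm only, could reveal allocation to the blinded statistician, so the handling of the codes needs to be planned.

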### Qualitative analysis

Qualitative data will be analysed using thematic analysis within NVivo software.^63^ A collaborative approach throughout the analytical process in which emerging themes are discussed between those who collect data and other members of the research team will enhance reflexivity and validity.^64^ The views and experiences of each group (children/young people, parents/caregivers, trial therapists) will be analysed both separately and in comparison with each other in order to gain a multiperspective view of the acceptability and feasibility of delivering CT-PTSD in routine NHS child and youth mental health services. Both commonalities and variations within and between these stakeholder groups will be explored.

### Health economic evaluation

Economic evaluation will compare CT-PTSD with TAU at the 11-month follow-up. It will take the NHS/personal social services perspective, preferred by the National Institute for Health and Clinical Excellence (NICE),^65^ but will additionally include education services, given the age of the population. Service use data will be collected using the CA-SUS while health-related quality of life will be assessed using the EQ-5D-Y (see above). Data on CT-PTSD contacts and TAU (CAMHS) contacts and on indirect time for the intervention (eg, supervision, training) will be collected directly from therapists/clinicians and service records; participants will be asked not to mention any CAMHS/mental health contacts so as to reduce the possibility of unblinding and double-counting of service contacts. Service use estimates will be combined with standard UK sources for unit costs to estimate total costs (including NHS reference costs for hospital contacts, the British National Formulary for medications and the Personal Social Services Research Unit Costs of Health and Social Care). The cost of CT-PTSD will be directly calculated.^66^

Economic analysis will be carried out on an intention-to-treat basis using an analysis plan to be drawn up prior to data analysis. Costs and outcomes will be compared and presented in terms of mean differences and 95% CIs obtained by non-parametric bootstrap regression to account for the non-normal distribution commonly found in economic data.^67^ Cost-effectiveness will be assessed through the calculation of incremental cost-effectiveness ratios (ICERs) (the additional cost of one intervention compared with another divided by the additional effects). The primary analysis will focus on effects measured using the CRIES-8, known to be sensitive to change in this population. Secondary analyses will explore cost-effectiveness in terms of QALYs derived from the EQ-5D-Y and using the area under the curve approach,^68^ a more policy relevant measure that is preferred by NICE, but with unknown sensitivity in young people with PTSD. Uncertainty will be explored using cost-effectiveness planes and cost-effectiveness acceptability curves based on the net-benefit approach.^69 70^ These curves are an alternative to CIs around ICERs and show the probability that one intervention is cost-effective compared with the other, for a range of values that a decision-maker would be willing to pay for an additional unit of an outcome. All economic analyses will be adjusted for baseline CRIES-8 score and site, in line with the clinical analyses, plus baseline values of the variables of interest (cost, QALYs), to provide a more relevant treatment effect estimate.^71^

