#### Health economic evaluation measures

Resource use will be collected using the Child and Adolescent Service Use Schedule (CA-SUS),^50^ modified for a PTSD population, a structured economic interview for youth mental health populations. The CA-SUS will be administered by trial team members at baseline and trained assessors (blinded to allocation) at post-treatment and 11-month follow-up assessments. The interview involves both the young person (if aged 12 years or below) and the young person’s primary parent/caregiver. Effectiveness will be measured using the youth version of the EuroQol measure of health-related quality of life (EQ-5D-Y),^51^ a preference-based, generic measure capable of generating quality-adjusted life years (QALYs).

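### Participants are asked to withhold a wider class of mental health contacts than the protocol says service records will supply

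*Protocol article*

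**What the plan says.** The protocol article divides resource-use data between two sources.

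- **Interview.** Under Health economic evaluation: "Service use data will be collected using the CA-SUS while health-related quality of life will be assessed using the EQ-5D-Y". Under Health economic evaluation measures, the CA-SUS is "administered by trial team members at baseline and trained assessors (blinded to allocation) at post-treatment and 11-month follow-up assessments".
- **Therapists and records.** Under Health economic evaluation: "Data on CT-PTSD contacts and TAU (CAMHS) contacts and on indirect time for the intervention" (supervision and training are the examples given) "will be collected directly from therapists/clinicians and service records".

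The boundary between the two is set by an instruction to participants: "participants will be asked not to mention any CAMHS/mental health contacts so as to reduce the possibility of unblinding and double-counting of service contacts".

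On scope, the same section says of the evaluation: "It will take the NHS/personal social services perspective", and of the perspective: "but will additionally include education services, given the age of the population". The comparison is made at the 11-month follow-up.

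On the experimental arm, the Interventions section says: "Following the completion of a course of CT-PTSD, usual NHS care arrangements will apply for participants in this arm".

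**The concern.** A split between interview and records works only if each relevant contact falls on one side or the other. Here the instruction takes out CAMHS and mental health contacts generally, while the list of what records put back is narrower. A contact that is suppressed in the interview and not on the record list is costed nowhere.

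Cost-effectiveness relative to TAU is a stated secondary objective with its own hypothesis (Objectives section). Incremental cost feeds every ICER, cost-effectiveness plane and acceptability curve. This is also a rule about collection. The economic analysis plan, which is still to be drawn up before data analysis, cannot recover contacts that families were asked not to report and that nobody extracted.

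**Working it through.** The documents give no unit cost, contact count or share of mental health care delivered outside CAMHS. The check is therefore a comparison of text, with one short piece of algebra.

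**Step 1. The two lists side by side**

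| Type of contact | Withheld from the CA-SUS? | Named as coming from therapists/records? |
|---|---|---|
| CT-PTSD session | Yes | Yes |
| CAMHS contact, TAU arm | Yes | Yes |
| CAMHS contact after CT-PTSD, CT-PTSD arm | Yes | Unclear: the label is TAU (CAMHS) |
| Mental health contact with another NHS, social care or education provider | Yes, read literally | No |
| Hospital, social care or education contact not about mental health | No | Not needed: CA-SUS |
| Medication | No: not a contact | Not needed: costed from the British National Formulary |

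Rows three and four are the problem. The other rows are consistent.

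**Step 2. Are row-four contacts in scope?** Yes. The perspective covers the NHS, personal social services and education. The TAU section allows help from mental health professionals and from others. Age may also move a participant between services. Entry is allowed up to age 17 and the horizon is 11 months, so anyone older than 17 years 1 month at randomisation (18 years − 11 months) turns 18 before the economic endpoint.

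**Step 3. How long is the row-three window?** Post-treatment is at about 5 months and the economic comparison is at 11 months (Participant timeline; Health economic evaluation). That leaves about 11 − 5 = 6 months in which CT-PTSD participants may receive ordinary care.

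**Step 4. Do the stated reasons require the wider instruction?** Two reasons are given.
- *Double-counting.* This can arise only for a contact that records also capture. It gives no reason to suppress one that they do not.
- *Unblinding.* The Recruitment section requires both a CT-PTSD therapist and a separate TAU clinician to be available within the recruiting team. An instruction limited to the participating service would still withhold the contacts most likely to reveal the arm.

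**Step 5. Effect on the result.** Let U be the mean cost per participant of contacts that neither source captures. Then

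recorded incremental cost = true incremental cost − (U in CT-PTSD − U in TAU).

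If U is equal in the two arms, total costs are too low in both but incremental cost is unbiased. If U differs, incremental cost is wrong by that difference, and the ICER is wrong by that difference divided by the incremental effect. The documents give no value for U in either arm, so neither the size nor the sign can be computed.

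**The case against.** The strongest reply is that the instruction is shorthand. Participants come from CAMHS and youth mental health services (Study setting), and the wording may mean just those services. The aim of avoiding double-counting fits this, because it presupposes that withheld contacts are captured elsewhere. On that reading the two lists nearly coincide. The reading is possible, but it sits badly with the word any, and the instruction is addressed to young people and caregivers, who could well apply it to a school counsellor or a crisis visit. If the narrow sense is intended, the wording still needs correcting.

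Second, an article condenses a fuller protocol, and the modified CA-SUS, the assessor script and the extraction forms are not shown. That limits what can be concluded about actual practice. It does not remove a mismatch between two lists that the article itself states.

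Third, the label TAU (CAMHS) may mean usual CAMHS contacts in either arm, and the economic analysis is by intention to treat. This stands as a fair reading, so the CT-PTSD-arm point is an ambiguity and not an established gap.

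Fourth, keeping more contacts in a blinded interview carries some risk. TAU may include supportive counselling or family therapy and may come from others, so a reported contact could hint at allocation. This stands in part: the risk is small once the participating service's contacts remain withheld, but it is not zero.

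A reader might go further and infer that all mental health care outside CT-PTSD and CAMHS drops out of the costs. The documents do not support that. They do not say that nothing else is extracted, or which services' records are used. Medication is costed separately, and hospital contacts have their own unit-cost source, although mental health hospital contacts could still fall under the instruction.

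**Conclusion.** The point holds as an inconsistency in a stated data-collection rule. What participants are asked to withhold is wider than what records are said to supply, and equal extraction of CAMHS contacts in the two arms is not made clear. Followed literally, this could under-count costs, and it would bias incremental cost if the uncaptured use differs by arm.

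The conclusion rests on reading the instruction as written and on the record list being complete as named; the article confirms neither. A reader might infer that the cost of CT-PTSD is understated, or its savings missed. The documents give no ground for choosing between these, nor for any figure in pounds. The primary clinical analysis is untouched. The change is worth making because it is cheap and the missing contacts could not be recovered at analysis.

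**What to change.** Use one definition for both lists.

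1. Limit the instruction to contacts with the participating CAMHS or youth mental health service that are captured from records.
2. Keep all other mental health contacts in the CA-SUS.
3. Extract the participating service's contacts over the full 11 months in the same way in both arms, with CT-PTSD sessions flagged, so that ordinary care after CT-PTSD is counted as it is for TAU.
4. Remove any remaining duplicates at analysis.

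The cost is a reworded assessor script, a common extraction form and some de-duplication. A small unblinding risk remains. Administering the CA-SUS after the outcome measures reduces it within a visit, but does not protect a later visit if the same assessor returns.
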